### **3.1.5 Handling of excluded and dropped cases**

(1) Upon a subject's dropout, the supervising physician should inquire about the patient's reasons, record the last data, and complete the assessments that can be completed.

(2) For cases withdrawing due to adverse reactions or ineffective treatment, the supervising physician should take appropriate measures based on the actual conditions of the subjects.

(3) Fill out the "Treatment Completion Summary" and "Clinical Trial Completion Status" in the Case Report Form (CRF).

(4) All excluded or dropped cases should be analyzed for intention-to-treat at the end of the trial.

(Note: Intention-to-treat analysis (ITT) refers to including subjects in the effectiveness analysis of the group they were assigned to, regardless of whether they received the group's intended treatment.)

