### **3.1.6 Case termination criteria**

(1) Subjects who experience increased pain or other severe adverse reactions during the study, making it inappropriate to continue participation.

(2) Subjects who request to withdraw from the clinical study midway.

(3) Patients who are uncooperative and non-compliant with treatment, despite repeated explanations by the clinician.

(4) Researchers should record in detail the reasons and timing of withdrawal from the study; cases that have surpassed half of the treatment duration should be included in

the efficacy analysis.

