### **11.1 Statistical analysis content and methods**

#### **11.1.1 Statistical analysis sets**

##### **11.1.1.1 Efficacy evaluation data set**

(1) Full Analysis Set (FAS): Includes all randomized participants. For cases not observed throughout the entire treatment process, the last observed outcome (last observation carry-forward: LOCF) is carried forward to the point of data missing. The number of participants evaluated for efficacy at the endpoint is consistent with the number at the start of the study. Comprehensive efficacy analysis is conducted using the Per Protocol Set (PPS) and the Full Analysis Set.

(2) Per Protocol Set (PPS): Includes participants who complied with the study treatment protocol, primarily those who can be measured for key indicators and have no major violations of the study protocol. Analyses of demographic and other baseline characteristics and other efficacy indicators are conducted using the PPS.

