#### **11.1.4 Efficacy evaluation**

All efficacy evaluation data will be summarized separately according to the FAS and PPS sets, with the FAS set as the primary analysis method.

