#### **11.1.5 Statistical analysis methods**

This study utilizes SPSS 28.0 for the analysis of clinical data. Continuous variables with normal distribution will be expressed as mean  $\pm$  SD and continuous variables with non-normal distribution will be reported as median and interquartile range (IQR).

For analyzing demographic data, continuous variables will be analyzed using the independent samples t-test or the Wilcoxon rank sum test depending on whether or not they conform to a normal distribution. Categorical variables will be analyzed using  $\chi^2$  test or Fisher's exact test. All significant demographic differences will be included as covariates in subsequent efficacy analyzes. The primary outcome indicator will be analyzed using analysis of covariance with baseline pain levels as a

covariate and group as a factor. The secondary outcomes, including changes in pain intensity at other time points (2, 5 minutes) and ROM at different time points, will be analyzed using repeated measures ANOVA or Mann-Whitney U test, depending on the data's distribution. Additionally, correlations between pain VAS scores and efficacy expectation scores will be explored using Spearman's or Pearson's correlation analysis. We will follow the intention-to-treat (ITT) principle and analyze all participants who receive treatment. Missing data of withdrawn participants will be processed using chained-equation multiple imputation.

(1) Case Distribution: Size of different data sets in each group, distribution of cases across centers, detailed list of dropouts, discontinuations, and reasons.

(2) Comparability Analysis: Compare demographic data and other baseline values to assess comparability between groups.

(3) Compliance Analysis: Compare whether patients in each group followed the design protocol. Compliance is evaluated based on the records in the participant's CRF form, calculating percentages for <80%, 80%–100%, and >100% compliance.

(4) Factors Affecting Efficacy Analysis: If there are significant differences between groups before the study or factors significantly affecting efficacy, these factors should be considered as covariates in the group comparisons, requiring covariance analysis or logistic regression, and a detailed list of concomitant medication use.

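### Sections 11.1.5 and 3.1.6(4) contradict the all-randomised primary efficacy set, and 3.1.6(4) can leave out participants because of their pain outcome

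*Protocol*

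**What the plan says.** Three places in the protocol agree on who is analysed:

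- 11.1.1.1 (Efficacy evaluation data set) defines the set: "Full Analysis Set (FAS): Includes all randomized participants". It adds that the number evaluated at the endpoint matches the number at the start.
- 11.1.4 (Efficacy evaluation) summarises all efficacy data on the FAS and the PPS, "with the FAS set as the primary analysis method".
- 3.1.5(4) (Handling of excluded and dropped cases) says "All excluded or dropped cases should be analyzed for intention-to-treat at the end of the trial". Its note defines ITT as analysis in the assigned group, whatever treatment was actually received.

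Three statements do not fit:

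- 11.1.5 (Statistical analysis methods), shortly after specifying the primary ANCOVA: "We will follow the intention-to-treat (ITT) principle and analyze all participants who receive treatment".
- 3.1.6(4) (Case termination criteria), on participants who stop: "cases that have surpassed half of the treatment duration should be included in" the efficacy analysis.
- 11.1.1.1, in the PPS definition: analyses of baseline characteristics and "other efficacy indicators are conducted using the PPS".

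**The concern.** The 11.1.5 sentence uses the ITT label for an all-treated population, contrary to the protocol's own definition of ITT in 3.1.5. Anyone randomised who never starts treatment is in under one section and out under the other.

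The 3.1.6(4) clause matters more. A half-way threshold has no function if every terminated case is analysed, so the natural reading is that earlier stoppers are not. Section 3.1.6(1) lists increased pain among the grounds for termination, and 5.4.1 makes change in pain the primary outcome. A participant could therefore leave the analysis because of a poor result on the endpoint itself. Such an exclusion after randomisation no longer compares the groups as randomised.

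With these statements side by side, a later choice between all randomised, all treated, or only those past half of treatment could each cite protocol text.

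**Working it through.** **Who is in under each statement.**

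| Participant | FAS (11.1.1.1, 11.1.4) and 3.1.5(4) | 11.1.5 | 3.1.6(4) |
|---|---|---|---|
| Randomised, never treated | in | out | not addressed |
| Treated, stops in first half | in | in | out, by implication |
| Treated, stops in second half | in | in | in |
| Completes | in | in | in |

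Section 11.1.5 goes on to impute missing data of withdrawn participants, which confirms that treated early stoppers stay in under that section. Only 3.1.6(4) removes them. Section 4.3 gives one session with 10 minutes of needle retention; taking that as the treatment duration, half is 5 minutes.

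**The plan's own figure.** Inputs from 2.2: changes 4.6 and 2.7, SD 1.0, margin 1.3, one-sided alpha 0.025, power 0.90, K = 1.

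n = (1.960 + 1.282)² × 1.0² × 2 / (4.6 − 2.7 − 1.3)² = 58.37 per group

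The protocol states 58. Then 58 / 0.92 = 63.04, so 64 per group and 128 in total, as stated. This calculation does not involve the analysis set, so the contradiction changes no stated figure.

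**How far the 3.1.6(4) exclusion could move the result.** Let d be the share of an arm stopping in the first half, m the mean change of those kept, and x the mean change of those who stop. Then

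shift from exclusion = d_AA × (m_AA − x_AA) − d_SAA × (m_SAA − x_SAA)

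If both arms lose the same share with the same shortfall (m − x), the shift is zero. For illustration, assume m = 4.6 and 2.7 (from 2.2) and x = 0, meaning early stoppers have no change in VAS. The protocol gives neither d nor x; both are assumptions. With exclusion the difference is always 4.6 − 2.7 = 1.90. With all randomised participants counted:

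| d | Early stoppers in AA only: 4.6(1 − d) − 2.7 | Shift from exclusion | Early stoppers in SAA only: 4.6 − 2.7(1 − d) | Shift from exclusion | Same d in both: 1.9(1 − d) | Shift from exclusion |
|---|---|---|---|---|---|---|
| 2% | 1.81 | +0.09 | 1.95 | −0.05 | 1.86 | +0.04 |
| 4% | 1.72 | +0.18 | 2.01 | −0.11 | 1.82 | +0.08 |
| 8% | 1.53 | +0.37 | 2.12 | −0.22 | 1.75 | +0.15 |
| 16% | 1.16 | +0.74 | 2.33 | −0.43 | 1.60 | +0.30 |

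At 8% in AA only (0.08 × 64 ≈ 5 participants), the excess over the 1.3 margin is 0.23 when they are counted and 0.60 when they are not. The equal-share columns are small but not zero, because a zero change is a larger shortfall from 4.6 than from 2.7.

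**PPS sentence.** Section 11.1.1.1 puts other efficacy indicators on the PPS; 11.1.4 makes the FAS primary for all efficacy data. For secondary outcomes both cannot govern.

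**The case against.** The strongest reply is that the primary set is already settled. It is defined in 11.1.1.1, named in 11.1.4 and supported by 3.1.5(4), so the conflicting sentences are strays that a careful analyst would override. That is largely right, and it limits the point.

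- **The PPS as a rival primary population.** A reader might infer this from 11.1.1.1. No section makes the PPS primary, and 11.1.4 ranks the FAS above it. What remains is the one sentence on other efficacy indicators.
- **More than one rule removing early failures under an ITT or efficacy label.** A reader might infer this by grouping 11.1.5 or the PPS with 3.1.6(4). The 11.1.5 wording loses only untreated people, and the PPS is a separately labelled set that is not called ITT. Only 3.1.6(4) has this effect.
- **Exclusion as explicit text.** Section 3.1.6(4) is worded as an inclusion. That earlier stoppers are left out is a strong inference. It gains some support from 9.3, which aims to analyse at least 80% of those entering and so envisages a reduced set.
- **Every early stopper as a treatment failure.** Withdrawal requests and non-compliance are also grounds in 3.1.6(2) and (3), so exclusion can depend on outcome but need not.
- **Few people affected.** With one 10-minute session the sets may differ little. If changes were normal with the planning means and SD, the chance of a negative change would be about 0.000002 in AA and 0.0035 in SAA (about 0.2 of 64). This stands as a caution on size. It concerns the 10-minute change, though, and does not give the rate of stopping in the first 5 minutes for any reason.

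**Conclusion.** The contradiction is in the text. Sections 11.1.5 and 3.1.6(4) cannot both be followed alongside the all-randomised FAS and the ITT rule in 3.1.5(4). The 3.1.6(4) clause, read in the only way that gives its threshold a purpose, allows an exclusion after randomisation that can depend on the primary outcome.

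The size is unknown. It rests on early-stopping rates and outcomes that the protocol does not give, and the figures above are conditional illustrations. A reader might conclude that the rule favours acupuncture, since only that arm's needle pierces the skin; the documents do not support a direction, and losses in the sham arm would bias the other way.

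This should be fixed before the analysis. It is not a fatal fault, because the primary set is named and the stated sample size is unaffected.

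**What to change.** 1. In 11.1.5, replace *who receive treatment* with *who are randomised, in their assigned group*.
2. In 3.1.6(4), delete the half-treatment clause on efficacy inclusion and keep the recording of reasons and timing. The termination criteria themselves need no change for this purpose.
3. In the PPS definition in 11.1.1.1, amend the last sentence so that the FAS is primary for all efficacy outcomes and the PPS is supportive.
4. Obtain the 10-minute VAS from participants who stop early, where possible. Section 3.1.5(1) already asks for the assessments that can still be completed.

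Items 1 to 3 cost wording only; item 4 adds one short assessment for a participant who stops early and is willing. Because early stoppers are then retained, their contribution will depend on the missing-data rule. Section 11.1.1.1 gives last observation carried forward and 11.1.5 gives chained-equation multiple imputation; that separate conflict should be settled in the same amendment.

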#### **11.1.6 Adverse events**

All adverse events (AEs) occurring during the study must be recorded and reported, and timely and appropriate measures must be taken for participants. Researchers must inform participants to honestly report changes in their condition after treatment, avoiding leading questions. During the observation of efficacy, pay attention to adverse events. If adverse events such as fainting, pain at the acupuncture site, bleeding, hematoma, or infection occur during acupuncture, participants will receive recorded and timely proper treatment until fully recovered.

Regardless of whether adverse events are related to the treatment method of the study, they must be thoroughly recorded, including the time of occurrence, symptoms, signs, severity, duration, laboratory indicators, treatment methods and outcomes, course, follow-up time, etc., and analyze the causes of adverse events.

(1) Serious Adverse Event Determination: Serious Adverse Events (SAEs) refer to unforeseen clinical events occurring during the study period, including patient death,

life-threatening situations, resulting in hospitalization, prolonging hospital stay, long-term or significant functional impairment/disability, or requiring medical or surgical treatment to prevent serious consequences.

(2) Handling of Adverse Events: AEs occurring during the study will be summarized by total number, system organ class (SOC), or other terms, summarizing at least once occurring event incidence. AEs will also be summarized by severity and relatedness to acupuncture. SAEs leading to study discontinuation will also be summarized.

For each count and incidence, each participant is counted only once regardless of the number of occurrences. When summarizing adverse events, missing severity ratings or causality assessments will be classified as "serious" and "definitely related."

All AEs will be presented in lists, including SAEs leading to study discontinuation due to acupuncture, and events leading to fatal outcomes. Missing values and incomplete dates in the lists will be displayed consistent with original records.

## **12 Ethical principles**

### **12.1 Ethical review**

This study project must be reviewed and approved by the institutional ethics committee before the clinical study can commence.

### **12.2 Benefits and risks**

Participants in this study project will be informed about the content of the clinical study, including its purpose, methods, and procedures such as treatment methods, grouping, and testing items. During the study, participants will receive AA or SAA

and undergo free examinations related to the project. Adverse events, such as fainting, pain at the acupuncture site, bleeding, hematoma, or infection during acupuncture, will be recorded and properly addressed until fully resolved.

Participants' personal data must be kept confidential. Participation in the clinical study is completely voluntary, and participants can withdraw at any stage without facing discrimination or retaliation, and their medical treatment and rights will not be affected. If any damage related to the clinical study occurs, participants will be entitled to appropriate compensation.

### **12.3 Informed consent**

(1) Researchers must familiarize themselves with and verify the comprehensiveness and compliance of the informed consent form (including ethical committee approval and adherence to the rights and duties of participants as stipulated in the Declaration of Helsinki) before discussing with participants and their families. Any amendments to written materials or the informed consent form must be approved by the ethics committee before re-obtaining informed consent from participants.

(2) The informed consent document should be explained to participants in clear and understandable language, including the purpose of the study, procedures, duration, examinations, expected benefits, and potential risks. Efforts should be made to avoid technical jargon to ensure participants fully understand the consent content.

(3) Participation in the study is voluntary, and participants have the right to withdraw at any time without discrimination or retaliation, and their medical treatment and rights will not be affected.

- (4) All personal data of participants involved in the study are confidential.
- (5) Participants may be assigned to different groups within the study.
- (6) Participants must be informed that the clinical trial treatment is provided free of charge and has been tested and approved. In case of study-related harm, participants are entitled to treatment and compensation. Participants can lodge complaints with the hospital's clinical research office or the ethics committee if they have concerns about the study process.
- (7) Participants and their families should be given sufficient time and opportunity to ask about the study details and any other related questions, ensuring they have fully understood the information before volunteering without coercion, undue pressure, or inducement.
- (8) The informed consent form should be signed and dated by the participant and their family members; for participants who are unable to perform legally relevant actions, their legal representative (including family members) must sign and date the form.
- (9) The researcher or their representative must also sign and date the informed consent form, indicating that they have explained the steps of the study and the potential risks and benefits to the participant.
- (10) If necessary (e.g., if the participant and their legal representative are illiterate), a witness should be present throughout the informed consent process. After a detailed explanation of the informed consent document, the witness should sign and date the form to confirm that the verbal consent matches the written consent.
- (11) The signing of the informed consent should occur before any research procedure

is performed. If the consent cannot be signed before the study due to justifiable reasons, it should be signed as soon as possible, and the form should note the date and explanation for any amendments.

(12) Two copies of the signed and dated informed consent form should be made; one copy is given to the participant or their legal representative, and the other is kept by the researchers for archiving.

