# **1. Background and purpose of the study**

Acute lumbar sprain (ALS) is a common musculoskeletal disorder, often caused by the abrupt overstretching of the muscles, fascia, and ligaments in the lower back due to external forces. It is characterized by severe pain and activity limitation in the lower back, which significantly impacts the patient's work and life. Therefore, quickly relieving symptoms in a short period of time is the main need of patients visiting the clinic.

According to the guidelines of the American College of Physicians, nonsteroidal anti-inflammatory drugs (NSAIDs) are recommended as the first-line pharmacological treatment for ALS, with diclofenac being the most commonly used NSAID. A study has shown that diclofenac began to have effects at approximately  $0.6 \pm 0.05$  hours after administration, with peak analgesia at  $2.7 \pm 0.24$  hours. Despite the convenience of oral administration, the delayed onset of action and moderate analgesic efficacy of NSAIDs limit their clinical application to some extent. Furthermore, there is guidance suggesting that non-pharmacological therapies can be used as a priority treatment, highlighting the importance of non-pharmacological intervention studies.

Auricular acupuncture (AA), as a form of traditional acupuncture therapy, offers potential advantages in pain management. Due to its simple treatment modality and rapid onset of action, it is particularly suitable for acute pain disorders in clinical practice. A previous study has shown significant pain relief with AA for lumbar pain, but limited efficacy for lumbar mobility disorders. Exercise therapy, commonly

utilized in the management of mobility disorders, has shown good efficacy for low back pain when combined with AA, significantly improving pain and function. However, there is a lack of rigorous randomized controlled trials to support the combination of AA with active exercise in the treatment of ALS, and further studies are required.

In this study, 128 patients with ALS will be recruited as study subjects, and sham auricular acupuncture (SAA) as control to observe the immediate efficacy of AA combined with active exercise for ALS.

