**Fig 1 Location of acupoint**

### **4.2 Appliance selection**

(1) Auricular needles: Use Seirin Corporation's single-use sterile microneedles, registration number: National Food and Drug Supervision and Medical Equipment (Import) No. 2012-2272550. Specifications are  $0.2 \times 1.5$  mm, see Figure 2A.

(2) Sham auricular needles: Same Seirin Corporation single-use sterile microneedles, registration number as above. Placebo needles look identical to real needles but lack a needle body and do not penetrate the skin, see Figure 2B.

[figure not shown]

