### **5.4.2 Secondary outcomes**

(1) Changes in pain intensity at 2 and 5 minutes after treatment will also be measured using VAS scores.

(2) Lumbar range of motion (ROM) will be assessed at baseline, 2, 5, and 10 minutes during treatment. Participants will be instructed to stand with their feet slightly apart, shoulder width apart, and their body relaxed. Measurements will be taken for forward flexion, backward extension, right lateral flexion, and left lateral flexion in order.

(3) Patient expectations of treatment outcomes will be assessed at baseline using the efficacy expectations scale.

(4) The success of the blinding will be assessed at the end of treatment using a blinded questionnaire.

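### Section 12.3(6) requires participants to be told that the trial treatment is tested and approved, without saying what, by whom or for what use; in plain language this conflicts with the rationale in section 1

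*Protocol*

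**What the plan says.** Section 12.3(6) of the protocol sets a mandatory statement for consent: "Participants must be informed that the clinical trial treatment is provided free of charge and has been tested and approved". The rest of that item deals with harm, compensation and complaints. No qualifier is attached to the testing or the approval.

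The evidence is described in section 1. On the treatment under study it says "there is a lack of rigorous randomized controlled trials to support the combination of AA with active exercise in the treatment of ALS" and calls for further studies. It also reports some earlier support: "A previous study has shown significant pain relief with AA for lumbar pain, but limited efficacy for lumbar mobility disorders". It adds that exercise combined with auricular acupuncture (AA) has done well in low back pain.

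Two other places mention a registration or an approval:

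- Section 4.2 gives a registration number for the real needle: "Use Seirin Corporation's single-use sterile microneedles, registration number: National Food and Drug Supervision and Medical Equipment (Import) No. 2012-2272550". The sham entry begins "Same Seirin Corporation single-use sterile microneedles, registration number as above" and continues "Placebo needles look identical to real needles but lack a needle body and do not penetrate the skin".
- Section 12.1 says "This study project must be reviewed and approved by the institutional ethics committee before the clinical study can commence".

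On timing, section 12.3(11) places the signature before any research procedure, with an exception for justifiable reasons. Section 5.4.2(3) says "Patient expectations of treatment outcomes will be assessed at baseline using the efficacy expectations scale". The primary outcome in section 5.4.1 is the VAS change from baseline to 10 minutes.

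**The concern.** A patient in acute pain who hears that the treatment has been tested and approved is likely to conclude that it is known to work for the present complaint. The trial exists because that is not known, and under 1:1 allocation half of those who hear the sentence will receive a non-penetrating device.

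Two things are at stake. The first is the accuracy of what people are told when they agree to take part. The second is measurement: the assurance would normally be given before the expectation scale is completed and before a self-reported pain score, so it may shift both. Section 11.1.5 plans to correlate expectation scores with VAS, and section 2.1 names before-and-after change within each group as an aim. Both would then partly reflect the assurance.

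**Working it through.** No figure in the protocol depends on this sentence, so the main check is to compare the passages.

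**1. What could the phrase refer to?**

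| Possible referent | Where | Does it cover the clinical trial treatment? |
|---|---|---|
| Registered needle | 4.2 | Only in part. It concerns a device; section 4.3 defines the treatment as needling plus guided exercise. |
| Ethics approval | 12.1 | No. It concerns the study project, and ethics review does not make a treatment tested. |
| Earlier studies of AA, and of AA with exercise | 1 | In part for testing, in lumbar or low back pain. They are not approval, and section 1 says rigorous trials of the combination in ALS are lacking. |
| Evidence for the sham as a treatment | none | Nothing is given. |

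No row supports both halves of the claim for the treatment as delivered in this trial. The plain reading therefore conflicts with section 1, and the narrower readings are not what the sentence says.

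**2. Who hears it?** All participants: 128 planned at 1:1, so 128 / 2 = 64 per arm.

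**3. What would a shared rise in expectancy do?** Section 2.2 assumes mean VAS falls of 4.6 (AA) and 2.7 (sham). Let e be an equal extra fall in both arms; its size is unknown.

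- Within groups: 4.6 + e and 2.7 + e. Both are inflated by e.
- Between groups: (4.6 + e) − (2.7 + e) = 1.9. This is unchanged.

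An equal shift therefore affects the within-group aim and leaves the randomised contrast as it was.

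**4. Does sample size depend on it?** The section 2.2 formula with SD 1.0, one-sided α 0.025, β 0.1 and margin 1.3 gives

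n = 2 × (1.960 + 1.282)² × 1.0² / (4.6 − 2.7 − 1.3)² = 21.01 / 0.36 ≈ 58.4 per group.

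The protocol states 58; strict rounding up gives 59. Then 58 / (1 − 0.08) = 63.04, or 64 per group and 128 in total, as stated. The consent wording enters none of these inputs.

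**5. Expectation scores.** They are collected at baseline, normally after consent. If the assurance pushes many scores towards the top of the scale, their spread narrows and the planned correlation weakens. This is a plausible direction; the documents give no means of sizing it.

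**The case against.** The best defence is that the sentence never mentions efficacy. It sits in an item about cost, compensation and complaints, and may refer loosely to the registered needle or the ethics-approved project. Section 1 says rigorous trials of the combination are lacking, which is not the same as saying that the treatment is untested. This makes the phrase ambiguous, and the conflict does depend on the plain-language reading. But section 12.3(2) asks for wording that participants can readily understand, and a narrow meaning that the sentence does not state cannot be expected to reach them.

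A reader might infer three stronger conclusions. The documents do not support them.

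- **That the statement cannot be true of the sham.** Section 4.2 lists the sham under the same registration number. Whether that registration extends to a version without a needle body cannot be settled here. What can be said is that the protocol offers no support for the sham as a tested treatment.
- **That consent is misinformed.** The consent form is not available. Sections 12.2, 12.3(2), 12.3(5) and 12.5 require disclosure of methods, grouping, benefits, risks and alternatives, and ethics review comes first. One potentially misleading sentence is as far as the text goes.
- **That the AA–sham difference is biased.** Both arms hear the sentence, and section 2.4 blinds participants and assessors. An unequal response is conceivable: with entry VAS of 4 to 8, someone entering at 4 cannot fall by 4.6, so AA may have less room for a further fall than sham. Failed blinding could also make the arms respond differently. Neither is demonstrated, and the documents give no basis for the size of any sham-only shift.

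**Conclusion.** The point holds as a consent-wording defect. An unqualified assurance that must be given to every participant goes beyond what sections 1, 4.2 and 12.1 support together. It is potentially misleading and should be corrected.

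The statistical consequence is limited. Expectancy may rise in both arms, affecting the expectation scores, their correlation with VAS and the within-group changes. That is an inference from the order of events, and its size is unknown. The sentence does not affect sample size or type I error, and with an equal response in two blinded arms the expected 1.9-point difference is unchanged.

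The conclusion assumes that participants take the phrase to describe the treatment they may receive, and that consent precedes the baseline scales as section 12.3(11) normally requires.

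**What to change.** In section 12.3(6), and in the consent form and script if they carry the same words, do one of the following:

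- delete the clause on testing and approval, keeping the statement that treatment is free; or
- limit it to what is documented: the needle's device registration and ethics approval of the study. If registration is mentioned, the sponsor should first confirm whether it extends to the sham version.

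In either case, add that the benefit of adding auricular needling to exercise for ALS has not been established, and that participants may be allocated to a sham. The same wording should be given to everyone before the expectation scale.

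Do not add a description of the sham's sensory features, such as whether it pierces the skin. That would give participants a cue for guessing their allocation in a trial that relies on participant blinding.

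The cost is a one-sentence amendment with ethics approval, and a few candidates may decline. Sample size and the planned analyses stay as they are.
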